## Physical Activity, CR and quality of life

Research unanimously supports the health benefits of PA in humans of all ages 109. It is proposed that increasing PA alone, even in the absence of modifying other health behaviors, will improve quality of life and prevent the onset of chronic disease 110,111. However, to date the only evidence that PA extends the life span is observational in nature 112. It is extremely difficult to determine if increased PA alone decreases mortality because changes in PA are typically associated with changes in body composition and other health-promoting behaviors such as nutrition and smoking cessation, although most studies have adjusted for these potential confounders. Other studies of PA programs without CR have found that increased exercise is generally associated with improved mood, energy, and quality of life. Based upon these findings, we hypothesized that the combination of 12.5% calorie restriction and 12.5% exercise would yield the greatest increases in mood and quality of life and would be associated with the lowest rate of attrition.

| **HYPOTHESES** |
| --- |

Caloric restriction (CR) from birth or during adult life in rodents and lower species prolongs life. Measurement of surrogate markers of longevity suggests that this may be the case in primates as well. The mechanism(s) responsible, and whether this is the case for humans is unknown. CR is associated with several well-known changes in metabolism, including lowering of the metabolic rate. It is unknown which, if any, of these adaptations might be responsible for extending maximum life span. One intriguing hypothesis is that CR lessens the oxidative damage and repair of vital tissues by reducing energy flux and metabolism. CR results in loss of weight and tissues, and lowers the rate of metabolism. A portion of this is the result of the reduced energy intake itself, and another portion is due to the decline in size of the metabolizing mass. Whether there is also a “metabolic adaptation,” defined here as a reduction of metabolic rate that is out of proportion to the decreased size of the respiring mass is a subject of continued debate.

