We will test for this, and in addition, if the expected decline in metabolic rate (whether or not proportionate to the respiring mass) that follows CR is associated with reduced oxidative stress in tissues, and risk factors for age-related metabolic diseases, including cardiovascular disease and type 2 diabetes. In addition, we will test if combining physical activity (PA) and CR to produce the same caloric deficit alters the adaptations caused by CR alone. As part of these investigations, we will assess the expression of genes involved in energy metabolism and oxidative stress that are known to be associated with longevity in “lower” organisms.

This study is to test if chronic CR, as it does in rodents and “lower” species and possibly in non-human primates, improves surrogate markers of longevity in humans, and therefore might extend the maximum life span. Thus, this is mainly a descriptive undertaking. However, we also propose to test several interesting hypotheses.

- **Hypothesis A**. Chronic CR (resulting in loss of weight and maintenance of energy balance at a new lower body mass) is associated with several metabolic adaptations, including lower absolute and relative rates of energy expenditure, lower body temperature, and evidence of lower tissue oxidative stress.

**Aims**: Measure and compare for difference:

**A1**) Energy expenditure (free living, sedentary 24-h, resting, exercise efficiency), and body temperature.

**A2**) DNA, protein and lipid oxidative damage.

- **Hypothesis B**. Chronic CR improves surrogate markers (risk factors) for chronic diseases, including cardiovascular disease and type-2 diabetes. These adaptations are the same whether the energy deficit is produced by combining PA and CR or by CR alone.

**Aims**: Measure and compare for difference:

**B1**) CVD risk factors (BP, lipid profile, hemostasis factors, homocysteine, endothelial function, and markers of inflammation).

**B2**) Type 2 diabetes risk factors. (Insulin action and secretion)

- **Hypothesis C**. Chronic CR dampens the activity of the neuroendocrine axes, and lowers SNS activity, potentially by decreased leptin signaling. These adaptations are less pronounced when the same energy deficit is achieved by combining PA and CR.

**Aims**: Measure and compare for difference:

**C1**) Hypothalamic neuroendocrine function (thyroid, adrenal, and somatotrophic axes), and diurnal rhythm of leptin.

**C2**) SNS activity

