Psychiatric Disorders: Participants will be screened using the Structured Clinical Interview for Diagnosis for the DSM-IV Axis I Disorders (SCID)113. Persons diagnosed with a lifetime history of psychotic disorders or Major Depression will be excluded. Subjects diagnosed with other psychiatric disorders will be excluded if it poses a threat to adherence to the protocol, as judged by the investigative team.

Eating Disorders: Participants will be screened for a history of anorexia nervosa, bulimia nervosa, and binge eating disorder 114 using the Interview for Diagnosis of Eating Disorders-Fourth Version (IDED-IV)115. Persons who are diagnosed with eating disorders (present or history) will be excluded from the study.

| **EXPERIMENTAL DESIGN** |
| --- |

Our primary hypothesis is that long-term CR that is associated with weight loss and maintenance at a new and lower weight decreases absolute and relative (adjusted for body weight and composition) energy expenditure, and decreases tissue oxidative stress. We also hypothesize that creating the same energy deficit by combining CR and PA will blunt these metabolic effects, but provide similar results in the surrogate markers used to assess cardiovascular disease and type 2 diabetes mellitus.

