## Overall Description of the Experiment

The proposed study is a 6 mo. study to be completed over a period of 2 yrs. The study will involve 60 overweight healthy male and female volunteers divided into four equal groups matched for age and gender. As shown in figure 1, the four groups include:

Group 1: Controls (No CR but receiving a healthy diet as per the American Heart Association recommendations)

Group 2: CR (energy deficit 25%)

Group 3: CR 12.5% + PA 12.5% (energy deficit 25%)

Group 4: CR (LCD 800 kcal balanced liquid diet) followed after a 15% wt. reduction by wt. maintenance (“wt. clamping”).

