**Figure 1**

; 6-

mo

Experimental Design

Time

0

1

2

3

4

5

6

mo

.

Control

25% CR

12.5%CR +

12.5% PA

LCD 800 kcal/d

-15% wt,

CR alone

Randomization

Feeding at PBRC

Green blocks denote metabolic test periods at baseline, 3 and 6 month periods (doubly labeled water plus 5-day inpatient stay (3 weeks total). Yellow blocks denote doubly labeled water measurements only (2 weeks).

This study is to test the feasibility and compliance to a 25% CR diet using several creative strategies, and to pilot and test several of the methods for a subsequent longer calorie restriction study. These include methods for assessing PA under free-living conditions, refinement of the assessments of the neuroendocrine axes, validation of the measure used to assess DNA oxidative stress, and final selection of the genes for tissue mRNA measurements. Because of the tight control of diet and exercise program, it will be impossible to blind all study personnel to the intervention assignment. However, most of the personnel performing the assessment measures (for ex. lab work, DEXA, energy expenditure etc.) will be blinded.

It is anticipated that compliance will be difficult for the volunteers and difficult to assess. Because of this, and in an attempt to improve the ease of compliance and to encourage it, all the volunteers will receive their meals at the Center for the initial 3.5 mos., and during the metabolic testing days. Compliance, however, will still be difficult to assess, since the measured parameters, including body weight, body composition, energy expenditure, dietary records, etc. are insufficiently precise or accurate to provide real-time objective information about it. Therefore, we have included a “weight clamped” group of subjects who have lost 15% of body weight by medically supervised LCD. This will allow the outcomes of interest to be assessed in a group of volunteers who will precisely maintain a new energy balance at an intake predicted to be 20-25% below their baseline energy requirements after rapid wt. loss (15%).

Screening of Subjects, Diet, Exercise Regimen and Behavioral intervention

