Subjects will be placed on an 800-kcal/d diet divided into 5 liquid portions (HEALTHONE). The diet will contain 70g of high quality protein, RDA of vitamins and minerals, 10g of fat with one meal and the remaining macronutrients as carbohydrate. Like the other 3 groups, subjects in this group will come to the metabolic kitchen every weekday to consume breakfast and dinner. The other liquid portions will be distributed daily to be consumed at home. Weekend meal replacements will be distributed Friday evening. Subjects will be seen in the clinic for measures of diet adherence, postural vital signs and metabolic weight once per week. Blood will be drawn and an electrocardiogram performed every 2 wks. If the chemistry panel shows potassium level below normal range, supplementation will be given. Upon achieving a 15% wt. loss, subjects will be progressively put back on solid food (same diet as other groups) in order to maintain the wt. loss. Subjects not attaining a 15% wt. loss by 14 wks. will be judged non-compliant and discharged**.**

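### The primary hypothesis concerns expenditure at a maintained lower weight, but only the weight-clamped arm has a maintenance phase; CR and CR+PA are tested under continued restriction

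*Protocol*

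**What the plan says.** Three places tie the primary question to a maintained lower weight. Hypothesis A (Hypotheses) is stated for "Chronic CR (resulting in loss of weight and maintenance of energy balance at a new lower body mass". The primary hypothesis (Experimental Design) says that "long-term CR that is associated with weight loss and maintenance at a new and lower weight decreases absolute and relative" energy expenditure. Outcome measures prefers the respiratory chamber because it is judged most likely to reveal changes in the expenditure needed to maintain weight.

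The arms are set out under Overall Description of the Experiment. Two are defined only by a percentage deficit: "Group 2: CR (energy deficit 25" per cent, and "Group 3: CR 12.5% + PA 12.5% (energy deficit 25" per cent. The third intervention arm alone has a second phase: "Group 4: CR (LCD 800 kcal balanced liquid diet) followed after a 15% wt. reduction by wt. maintenance". The text below Figure 1 says its members will "precisely maintain a new energy balance at an intake predicted to be 20-25% below their baseline energy requirements after rapid wt. loss (15" per cent).

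Nothing moves Groups 2 and 3 to balance. Their targets are set from baseline measurements (Diets and diet delivery; Exercise). Months 4-6 continue the prescribed plan (Timeline). Compliance is judged against an expected rate of weight loss with no end date (Individual tailoring of treatment). Follow-up chamber meals are set at 100%, 87.5% or 75% of baseline 24-hour expenditure by arm (Energy expenditure, Metabolic Chamber), although the urinary norepinephrine paragraph describes the chamber day as one of energy balance. The power section names CR and CR+PA as the interventions whose effect is tested.

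**The concern.** Someone on a fixed intake 25% below baseline need reaches balance only after losing enough weight for need to fall to that intake. If that has not happened by the test block, the measurement describes a person still losing weight, which is not the state in the hypothesis.

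The protocol treats this as material. In Hypotheses it says of the fall in metabolic rate that "A portion of this is the result of the reduced energy intake itself", attributes another part to lost mass, and asks whether there is adaptation beyond these. Adjusting for fat-free mass and fat mass deals with the mass part only. A lower adjusted expenditure under CR or CR+PA could then be reported as adaptation at a maintained lower weight when part of it is a response to current negative balance. The hood, labeled-water, body-temperature, leptin, thyroid and sympathetic measures carry the same ambiguity. The arm that does reach the hypothesised state is introduced because compliance is hard to assess, and is not named as the test of the maintenance clause.

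**Working it through.** **Plan's own figure.** The protocol prints no expected weight loss or residual deficit for Groups 2 and 3. Its only design figure for the primary endpoint is Table 2, which reproduces. For CV 5%, difference 10% and 11 per group, the SD of change is 5 × √2 = 7.07%. With three groups and minimal variability of means, λ = 11 × (10/7.07)²/2 = 11 on 2 and 30 df, giving power 81.3% against the stated 80%. The point below does not depend on it.

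**Inputs from the protocol.** Initial gap 25% of baseline need. Need 20-25% lower at 15% weight loss. Up to 10 weeks at 800 kcal/d to lose 15%, with a limit of 14 weeks. Testing at months 3 and 6 (taken as days 91 and 182). Menu levels 1800-3400 kcal/d.

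**Assumptions.** Baseline need lies in the menu range (no mean is given; the midpoint is 2600). Need falls linearly with weight. Weight loss is proportional to the energy gap. Adherence is full. The second route below also assumes 7700 kcal/kg, 70-90 kg and 2200-3000 kcal/d.

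**Weight loss needed for balance.** Slope k = 20/15 to 25/15 = 1.33 to 1.67% of need per 1% of weight. Balance at 75% of baseline intake needs 25/1.67 = 15.0% to 25/1.33 = 18.8% loss.

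**Time course.** Gap(t) = 25% × exp(−t/τ); loss(t) = (25 − gap)/k.

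*Worked case (80 kg, 2600 kcal/d, 7700 kcal/kg, k = 1.67).* Full loss is 0.15 × 80 × 7700 = 92,400 kcal and the initial gap is 0.25 × 2600 = 650 kcal/d, so τ = 142 d.
- Month 3: gap 25 × exp(−91/142) = 13.2%; loss (25 − 13.2)/1.67 = 7.1%.
- Month 6: gap 25 × exp(−182/142) = 6.9%; loss 10.8%, with about 0.16 kg/week still being lost.

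*Calibration to the protocol's diet time, without kcal/kg.* If 800 kcal/d gives 15% loss in T days and D = 100 × (1 − 800/need), then τ = −T/ln(1 − 15k/D). At 2600 kcal/d, T = 70 and k = 1.67: D = 69.2 and τ = 156 d, so the gap is 14.0% at month 3 and 7.8% at month 6.

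| Setting | Gap, month 3 | Gap, month 6 |
|---|---|---|
| 10 weeks, 2600 kcal/d | 14.0-16.0% | 7.8-10.3% |
| 10 weeks, 1800-3400 kcal/d | 11.5-16.9% | 5.3-11.4% |
| 7700 kcal/kg, 70-90 kg, 2200-3000 kcal/d | 10.7-17.0% | 4.6-11.6% |
| 14 weeks, 1800-3400 kcal/d | 14.3-18.9% | 8.2-14.2% |
| 6 weeks (assumed, most favourable) | 6.8-13.0% | 1.9-6.7% |

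In the 10-week settings, predicted loss is 6.0-8.3% at month 3 and 9.6-12.9% at month 6, against the 15.0-18.8% needed. No setting reaches balance by month 6.

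**CR+PA.** Intake is 87.5% of baseline need and exercise adds 12.5%, so the gap is 12.5 + 12.5 − k × loss = 25 − k × loss. This is the same equation if the exercise is done in full.

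**Weight-clamped arm.** Loss of 15% is expected within 10 weeks, but the rule is that "Subjects not attaining a 15% wt. loss by 14 wks. will be judged non-compliant". A block near week 13 may therefore come before, or soon after, the start of maintenance for some participants. By month 6 maintenance has had about 12 weeks even for someone finishing at week 14 (26 − 14).

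**The case against.** **The design already handles this.** The clamped arm exists so that the outcomes can be assessed at a new energy balance. This stands, and it limits the point. A reader might infer that the trial cannot test its primary hypothesis; the documents do not support that, because Group 4 versus control at month 6 can test it. What is missing is a statement that this contrast is the test.

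**The deficit is not a bias in expenditure.** A reader might set a residual gap of 5-11% against the planned 10% effect. These are different quantities: one is intake relative to need, the other a change in expenditure. The documents do not say how much a continuing deficit lowers expenditure, so the comparison should not be made.

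**Weight stability does not remove the effect of low intake.** The clamped arm also eats 20-25% below baseline need, and the protocol defines adaptation as a fall out of proportion to respiring mass, with no stability condition. This stands: maintenance removes ongoing negative balance, not low intake. The hypotheses nevertheless name the maintained state.

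**The month-6 figure depends on assumptions.** It does, down to 1.9% in the most favourable setting. Poorer adherence could bring balance sooner, though at a milder restriction than the one defined.

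**Month 3 matters less.** The simple analysis uses end-of-study change; month 3 enters through the repeated-measures model. The exact position of the block in Figure 1 cannot be read here, so the timing for the clamped arm is partly inferred.

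**The study is a largely descriptive pilot.** The protocol says so, and the wording of Hypothesis A could describe where chronic CR eventually leads. That softens the point, but the claim is still labelled the primary hypothesis.

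**Conclusion.** The mismatch is in the current text and concerns the primary hypothesis. Groups 2 and 3 have no maintenance phase. On the protocol's prediction of need at 15% loss, plus the listed assumptions, they are clearly in deficit at month 3 and probably at month 6. Month 3 holds in every setting tried. Month 6 is firm if the liquid diet takes 10-14 weeks to reach 15% and weaker if it takes 6.

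Their results can describe expenditure during continued restriction. They cannot by themselves support a claim about adaptation at a maintained lower weight. A reader might describe these arms as in a continuing 25% deficit; that is also wrong, because intake is fixed against baseline while need falls, so the deficit shrinks.

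**What to change.** 1. Name the weight-clamped arm versus control at month 6 as the test of the maintenance clause.
2. For Groups 2 and 3, reword Hypothesis A, the primary hypothesis and the endpoint rationale to refer to expenditure during continued restriction relative to baseline energy requirement, and make no weight-maintained adaptation claim from them. Reconcile the description of the chamber day as one of energy balance with the stated chamber feeding levels.
3. Use the day 0 and day 14 weights and DEXA scans of each labeled-water period, with the weekly weights, to report energy balance at each test block. Treat a month-3 block in the clamped arm as weight-maintained only if 15% loss was reached and weight was stable beforehand, with the stability cut-off fixed before analysis.

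The cost is wording and one derived variable from data already collected. The weight-maintained claim then rests on the 15 clamped participants, and the CR and CR+PA claim is narrower. On Table 2's own inputs the two-arm contrast remains workable: with 11 completers per arm, a 10% difference and SD 7.07%, the normal approximation gives Φ(10/(7.07 × √(2/11)) − 1.96) = Φ(1.36), about 91% power. No diet or clinical rule changes.

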## Outcome measures

**Primary outcome**. The primary endpoint will be the rate of energy expenditure under resting, sedentary and free living conditions. Each component will be assessed by state-of-the-art methods (ventilated hood, respiratory chamber and doubly labeled water). Sedentary energy expenditure in the respiratory chamber has been used for the power analysis. The reason is that this method is the most sensitive for assessing all of the components of daily energy expenditure, except for the cost of voluntary activity under free living conditions, and is therefore the most likely to uncover differences in energy expenditure for weight maintenance induced by chronic CR. As shown in Table 2, 5-11 subjects are sufficient to detect a 10% decrease in absolute or adjusted 24-h energy expenditure. Furthermore, assuming an intra-subject variability of 7.5%, a 15% decrease in total daily energy expenditure can be detected by doubly labeled water with only 11 subjects per group. With 15 subjects enrolled per arm in the study, we feel confident that we will have the necessary power of detecting significant decreases in both sedentary and total daily energy expenditure.

**Secondary outcomes**. While the proposed studies have sufficient power to detect differences for the primary endpoint, because of the novelty and opportunity offered by this study, we also plan to monitor several secondary outcomes of interest in a more descriptive manner. However, the methods and number of subjects may not always be up to the task of uncovering suspected differences.

1. Changes in body composition. We hypothesize that approximately 2/3 of wt. loss during CR will be fat mass, but more (75%) when a combination of CR and increased PA is the cause of similar negative energy balance. Body composition will be measured by DEXA, the new gold standard. Because of the precision and reliability of the method, small differences in changes in fat mass and fat-free mass can be detected.
2. Changes in oxidative stress. At baseline and at different phases of the study, oxidative stress will be measured indirectly by DNA damage, lipid peroxidation (isoprostanes), and protein carbonylation.

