3. *Changes in neuroendocrine activities*. The thyroid, somatotropic, and adrenal axes will be measured over 24 hrs. by blood sampling and compared to changes in leptin profile. Activities of the thyroid and somatotropic axes are hypothesized to decrease in response to CR, whereas the adrenal axis will increase. Differences in areas under the curve will be detectable with our number of subjects.
4. *Sympathetic nervous activity* is predicted to decrease in response to CR (spectral analysis of heart rate and urinary excretion of catecholamines).
5. *Changes in cardiovascular disease risk factors and insulin sensitivity/secretion.* We hypothesize that both CVD factors and insulin sensitivity will improve in a similar manner in the groups subjected to CR alone or a combination of CR+PA. Insulin secretion is not expected to change.
6. *Changes in* *tissue gene expression*. We will measure these changes in muscle and adipose tissues by quantitative RT-PCR. The aim of this endpoint is to test the hypotheses that CR alters the pattern of gene expression in adipose tissue and skeletal muscle such that: a) oxidative stress is reduced; b) energy is conserved, and; c) “ancient” genes associated with longevity are regulated in a fashion consistent with involvement in longevity from animal data.
7. *Changes in quality of life*.We hypothesize that subjects enrolled in these studies of CR or CR+PA will improve their quality of life because of weight loss. However, subjects enrolled in the CR+PA group will have a better quality of life than those in the CR alone group.

| **METHODS AND PROCEDURES.** |
| --- |

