In the final analysis we will investigate the change from baseline for all continuous variables. The analysis will be carried out in two different ways. Using an ANOVA method with treatment groups as fixed effect, we will do a simple analysis of end-of-study change from baseline. The second one is the more detailed and precise analysis using a mixed model approach considering a repeated measures design method with treatment groups and time as fixed effects and subject as random effect. The covariance matrix of the multivariate response for each subject will be modeled appropriately and estimated using the maximum likelihood method. The drop out rates will be compared across all treatment groups (3) testing for equality of proportions using the 2 test. For all analyses, SAS Version 8.1 (or higher) will be used.

| **Table 2**Within subject CV **(%)** | Detectable difference (% from baseline) | n/group | Total N at the end of the study | Power (%) |
| --- | --- | --- | --- | --- |
| Chamber method |  |  |  |  |
| 3 | 5 | 15 | 45 | 80 |
| 3 | 10 | 5 | 15 | 84 |
| 3 | 15 | 3 | 9 | 85 |
| 3 | 20 | 3 | 9 | 98 |
| 5 | 5 | 40 | 120 | 80 |
| 5 | 10 | 11 | 33 | 80 |
| 5 | 15 | 6 | 18 | 85 |
| 5 | 20 | 4 | 12 | 86 |
| Doubly labeled water method |  |  |  |  |
| 7.5 | 10 | 23 | 69 | 80 |
| 7.5 | 15 | 11 | 33 | 81 |
| 7.5 | 20 | 7 | 21 | 83 |

| **RISK / BENEFIT ASSESSMENT** |
| --- |

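### Hypothesis B asserts that CR and CR+PA have the same effect on cardiovascular and diabetes markers, but the plan only tests for difference, so small arms favour the claim

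*Protocol*

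**What the plan says.** In the protocol's Hypotheses section, Hypothesis B has two sentences. The first says chronic CR improves risk markers for cardiovascular disease and type 2 diabetes. The second says: "These adaptations are the same whether the energy deficit is produced by combining PA and CR or by CR alone". The aims listed directly below are introduced by "Measure and compare for difference", the same lead-in as for Hypotheses A and C.

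The claim appears twice more. The Experimental Design section expects the combined arm to blunt the metabolic effects "but provide similar results in the surrogate markers used to assess cardiovascular disease and type 2 diabetes mellitus". Item 5 of the secondary outcomes (Outcome measures) hypothesises that "both CVD factors and insulin sensitivity will improve in a similar manner" under CR alone and under CR+PA.

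For analysis, Power Calculation and Data Analysis covers all continuous variables in two ways: "Using an ANOVA method with treatment groups as fixed effect, we will do a simple analysis of end-of-study change from baseline", followed by a repeated-measures mixed model. On size, Outcome measures says "With 15 subjects enrolled per arm in the study", which agrees with 60 volunteers in four equal groups. Power Calculation and Data Analysis refers instead to 30 per group. Sample size was worked out for energy expenditure only.

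**The concern.** A difference test treats no difference as the default and can only reject it. If sameness is the hypothesis, failing to reject is the only outcome that looks favourable, and failing to reject is not evidence of sameness.

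This reverses the usual effect of low power. For Hypotheses A and C, which predict differences, small arms work against the investigators. For the second sentence of Hypothesis B, small arms work in its favour: the less precise the comparison, the more often the clause appears to be borne out.

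At stake is a conclusion that replacing half of the dietary deficit with exercise makes no difference to cardiovascular and diabetes markers, drawn from data that cannot exclude a sizeable difference either way.

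**Working it through.** **Inputs from the protocol.** 15 per arm and four arms (Outcome measures; Overall Description of the Experiment); 11 per group as the completer number in Table 2 for a 10% difference at 5% CV; 30 per group (Power Calculation and Data Analysis, in conflict with 15); alpha 0.05.

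**Assumptions.** The test is two-sided. The true CR+PA minus CR difference, d, is in units of the SD of change. The protocol gives no SD, effect size or margin for any cardiovascular or insulin marker, so a range of d is shown. All n subjects per arm are analysed, with error pooled over four arms (4n − 4 degrees of freedom).

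**Step 1: the plan's own figure.** Table 2 gives 80% power with 11 per group for a 10% difference at 5% within-subject CV. With SD of change = √2 × 5% = 7.07%, d = 10/7.07 = 1.414. For a three-group ANOVA with minimal variability of means, λ = n·d²/2 = 11 × 2/2 = 11, which gives power 81.3%. The other ten rows also reproduce to within two points. Table 2 is therefore a set of difference-test calculations for energy expenditure and does not bear on sameness of the Hypothesis B markers.

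**Step 2: precision of CR+PA minus CR.** 95% CI half-width = t(0.975, 4n − 4) × √(2/n).
- n = 15: 2.003 × 0.365 = 0.73 SD
- n = 11: 2.021 × 0.426 = 0.86 SD

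**Step 3: probability of a non-significant result.** Noncentral t with noncentrality d/√(2/n). At n = 15:

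| True difference (SD of change) | Noncentrality | Non-significant |
|---|---|---|
| 0.25 | 0.68 | 90% |
| 0.5 | 1.37 | 73% |
| 0.75 | 2.05 | 48% |
| 1.0 | 2.74 | 23% |

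For d = 0.5 at n = 15, a normal approximation gives 72.3% and a plain two-sample t test 73.8%, so the method hardly matters. At other sizes, d = 0.5 is non-significant in 79% of trials with 11 per arm and in 52% with 30 per arm. With 11 per arm, d = 0.75 is non-significant in 60%.

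**Step 4: could sameness be shown at this size?** Take an equivalence rule that requires the 90% CI to lie inside ±0.5 SD (an assumed margin). At n = 15 the expected 90% half-width is 1.673 × 0.365 = 0.61 SD, already wider than the margin. With a true difference of zero, the chance of success is under 1%. About 69 per arm would be needed for 80% power. With a margin of 1.0 SD, 15 per arm gives about 70%.

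**The case against.** The strongest reply is that the protocol never says a non-significant difference will be reported as sameness. A reader might infer that it plans to, but no text supports this. The Hypotheses section also poses the question as whether adding physical activity alters the adaptations to CR, and on that reading sameness is an expectation that a difference test tries to refute. The planned models also yield the estimates and intervals needed. This stands as far as intent goes, but the stated hypothesis is still one that the stated aim cannot support.

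Second, the limitation is largely disclosed. The study is called mainly descriptive, the secondary outcomes are to be monitored more descriptively, and the numbers are admitted to be possibly too few to reveal suspected differences. That limits the seriousness. It does not remove the problem: the protocol also says it will test hypotheses, and a warning about missing differences does not stop a missed one being taken as support for sameness.

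Third, a reader might treat the absence of an equivalence margin as an error in itself. It is not one here, because a margin or reporting rule could sit in a statistical analysis plan that is not shown. The point rests only on the mismatch between hypothesis and aim inside the protocol.

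Fourth, the half-SD difference is an assumption, and the calculation reflects the end-of-study ANOVA. Any gain from the mixed model cannot be quantified from the document. Both are fair, so 73% is one row of an illustration.

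**Conclusion.** The second sentence of Hypothesis B, and its counterparts in Experimental Design and secondary outcome 5, state a conclusion that the planned comparison cannot support. The first sentence of Hypothesis B suits a difference test and is not in question, nor is the primary endpoint.

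With 15 per arm, a non-significant result would leave differences of the order of 0.7 SD of change unexcluded, and half-SD differences would usually go undetected. The exact rates depend on the assumed true difference, two-sided alpha 0.05 and full completion; dropout makes them worse. The point survives the conflict over group size, since at 30 per group a half-SD difference is still missed about half the time. As these are secondary, avowedly descriptive outcomes, the correction should be made but does not threaten the main analysis.

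**What to change.** Restate the second sentence of Hypothesis B, and the matching text in Experimental Design and secondary outcome 5, as estimating CR+PA minus CR for each marker with its 95% CI. Add that a non-significant difference will not be reported as similarity. Reconcile the 15 and 30 per group.

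If a sameness claim is kept for any marker, it needs an absolute margin fixed before analysis. That margin should not be derived from this trial's own CR effect: the effect is unknown until the data are analysed, would be imprecise at this size, and gives no usable margin for insulin secretion, which secondary outcome 5 does not expect to change. The protocol should also acknowledge that 15 per arm has under 1% power for a margin of 0.5 SD.

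The cost is wording only, with no change to sample size, visits or treatment. The downside is a weaker permitted conclusion, usually that the two arms were not distinguished.
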